### Recruitment {15}

In total, 150 patients will be recruited in one German academic university hospital. Each patient who is scheduled for a Roux-en-Y bypass will be informed about the study and will be asked for his/her willingness to participate in the study to reach the target sample size. The total study duration is planned for 3 years (2 years for recruitment plus 1 year for the follow-up).

## Assignment of interventions: allocation

### Sequence generation {16a}

A statistician of the sponsor has prepared a computer-generated randomization list equally distributing both suture groups in a 1:1 ratio using different random block lengths unavailable to the clinic. The block sizes will not be disclosed, to ensure concealment. The randomization list is sealed and locked up at the sponsor site. Thus, the medical staff has no influence on the randomization. A stratification based on risk factors was not performed.

### Concealment mechanism {16b}

Patients will be randomized intraoperatively using opaque, sealed envelopes, containing the information of the random allocation of the device, a randomization fax, and the respective suture material (UBS or CS) in appropriate numbers and in different USP sizes to create the GJA as well as the JJA. The envelopes are prepared by the sponsor and provided to the clinic in sufficient numbers. The randomization envelopes are stored in the principal investigator’s office and individually carried to the operation theater for each surgery by the responsible surgeon. Assignment to the patients will be done in a chronological manner by the surgeon, according to a consecutive random number. Briefly after the construction of the GJA using the 45-mm linear stapler before suturing the enterotomy, the nurse will open the envelope and mention the randomization result to the operation team. After each surgery, the clinic has to send the included randomization fax to the sponsor to confirm the inclusion of a patient as well as the randomization result.

### Implementation {16c}

Before the start of the trial, an initiation visit was performed by the project management of the sponsor to inform and to instruct the involved medical staff on the specific study documents and procedures.

## Assignment of interventions: blinding

### Who will be blinded {17a}

Patients will be unaware of the type of suture material they receive to ensure a valid assessment of the postoperative outcome parameter, which they judge. It is impossible to blind the surgeon because, first, the suture type can be differentiated by configuration and feel, and second, the surgeon has to be aware of the suture type to perform the anastomosis. The statistician has no access to the eCRF or database. After data base closure, generation of the data export (performed by the data manager), and determination of the analysis population, the statistician responsible for the analysis will be unblinded.

### Procedure for unblinding if needed {17b}

An unblinding of the patients is not planned during the study, but if the patient has to be unblinded, e.g. because of serious adverse events, the patient will stay in the study and be analysed as planned. If the number of unblinded patients would be too high, maybe a subgroup analysis has to be performed, comparing blinded and unblinded patients.

## Data collection and management

### Plans for assessment and collection of outcomes {18a}

All participant data required based on the study protocol will be collected by the principal investigator or trained representatives and entered in a paper-based CRF provided by the sponsor.

Intraoperative documentation includes the following—the surgeon’s initials, surgeon’s position, randomization result (UBS or CS), and the use of antibiotic prophylaxis—and is performed for all study subjects.

In addition, the following parameters are mandatory and recorded and measured in all randomized patients during surgery:
Total operation durationEstimated blood lossIntraoperative blood transfusionSuturing time to create the gastro-jejunal anastomosisSuturing time to create the jejuno-jejunal anastomosisNumber of used threadsOutcome of the leak testHandling assessment of the suture materialDevice malfunctionsAdverse events

The EQ-5D-5L and BAROS self-assessment quality-of-life questionnaires will be filled in by the patients themselves. The completed CRFs and questionnaires will be securely stored in the principal investigator’s office, which is protected against unauthorized access.

### Plans to promote participant retention and complete follow-up {18b}

The schedule of the study visits corresponds to the standardized aftercare scheme of the hospital. To promote the adhesion of the patients, they are reminded by the involved study nurse of the follow-up appointments by telephone call. The collected data set of patients discontinuing the study prematurely will be analysed until their discontinuation. The reason for discontinuation (e.g. withdrawal from the trial, lost to follow-up) will be recorded.

### Data management {19}

The collected data recorded by the clinic on paper-based CRFs and by the patients on paper-based QoL questionnaires (EQ-5D-5L and BAROS) will be entered by the sponsor’s data management department in a timely manner into an electronic capture system (secutrial) owned by the sponsor. The data entry will be done after the data set has been checked by an authorized research monitor. After each monitoring visit, the responsible research monitor will forward the original paper-based CRF and the original paper-based EQ-5D-5L and BAROS questionnaires to the sponsor’s data management for data entry. The data entry will be performed by the responsible data managers (two different persons), not by the involved statistician. To ensure data quality and reliability, a double entry will be performed by the data management. Thereafter, the entered data will be checked for completeness, correctness, plausibility, and consistency by validating programmes, which thereby produce queries. All inconsistencies will be forwarded to the responsible investigator for clarification and explanation. The original CRFs will be stored at the sponsor’s site, and a copy will remain at the clinic’s site. The data will be archived for 10 years.

### Confidentiality {27}

Patient data will be handled confidentially and subjected to the data protection law. The principal investigator ensures that CRF or questionnaires transmitted to the sponsor do not contain personal patient data. Each patient will receive an individual patient study identification number (pseudonymization), and only the investigator will be able to identify a patient by the unique patient study identification number. A separate patient identification list will be set up and stored confidentially at the clinic site.

### Plans for collection, laboratory evaluation, and storage of biological specimens for genetic or molecular analysis in this trial/future use {33}

Not applicable, because no biological specimens will be collected in this study.

## Statistical methods

### Statistical methods for primary and secondary outcomes {20a}

The intention-to-treat principle will be applied for data analysis. A CONSORT diagram will be utilized to graphically display the eligibility, allocation, and follow-up course of the participants (**41**). Demographics, anamnesis, and baseline characteristics will be presented in a tabular form by treatment group. Continuous measures will be summarized by the number of non-missing observations, minimum, maximum, median, and mean with standard deviation, and categorical measures by absolute and relative frequencies.

The primary outcome measure is the suturing time to perform the GJA and JJA. The independent samples *t*-test with a two-sided significance level of 0.05 will be used for the comparison of treatment groups (UBS vs. CS). 95% CI will be provided to allow a quantitative evaluation of the treatment effect with respect to the minimum clinically relevant difference of 1.9 min. The secondary variables will be analysed descriptively.

The test regarding the primary variable is considered confirmatory; all other tests are explanatory. For the analysis of binary data, a chi-square test will be used; for nonparametric data, a *U*-test according to Wilcoxon–Mann–Whitney or to Kruskal–Wallis will be used; and a *t*-test or one-way ANOVA will be used for metric data, if a normal distribution is assumed. All statistical tests will be performed two-tailed with a pre-specified significance level of *α* = 5%. Two-sided 95% confidence intervals will be given, where appropriate.

The secondary outcomes include the following:
Pain (visual analogue scale, values from 0 to 100, 100—max. pain)Satisfaction (numeric scale values from 0 to 100, 100—best)EQ-5D-5L questionnaire: EQ index range from 1 best to 5 worse and EQ-VAS scale value (0–100—best).BAROS questionnaire, three sub-scores with a maximum of 3 points each (weight loss (% of excess), improvement of medical conditions and Quality of Life), and the total score with a maximum of 9 points (best).Length of hospital stay in daysHandling assessment of the suture material (different dimensions using a Likert scale with levels from 1 excellent to 5 worse).

The outcomes will be analysed descriptively and compared between suture groups and between visits, where appropriate.

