**Methods:**

The study will be performed as an industry-sponsored, mono-centre, randomized, active-controlled, two-arm, parallel-group, superiority trial. A total of 150 patients will be randomly allocated to both suture types in a 1:1 ratio. The suture material will be used to construct the gastro-jejunal anastomosis as well as the jejuno-jejunal anastomosis. The time needed to create both anastomoses is the primary endpoint. Intraoperative handling of both suture materials, patient satisfaction, pain, and complications occurring during the study will serve as secondary outcomes. Furthermore, the difference in quality of life using two different questionnaires (EQ5D5L and Bariatric Analysis and Reporting Outcome System (BAROS)) will be assessed preoperatively and postoperatively (30 days and 12 months) and will be compared between the suture groups as well as over time. The EQ-5D-5L questionnaire consists of five dimensions (mobility, self-care, usual activities, pain or discomfort, anxiety or depression) and a visual analogue scale (VAS) to record the patient’s health status. The BAROS evaluates three sub-categories: The percentage of excess weight loss, the changes in medical conditions, and quality of life, leading to three individual sub-scores, which are added to the final total score defining the failure or success of treatment. The follow-up period is 1 year after surgery.

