### Methods for additional analyses (e.g. subgroup analyses) {20b}

To identify relevant influencing factors (confounders), multivariate regression models will be considered. Depending on the outcome variable, linear or logistic models will be implemented, and the patient’s age, sex, BMI, and respective baseline values will be used as covariates to adjust for.

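### EQ index and EQ-VAS are measured before surgery, but the named between-arm tests leave that value out, and baseline-adjusted models appear only as optional additional analyses

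*Protocol article*

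**What the plan says.** The Abstract (Methods) says that quality of life, by EQ-5D-5L and BAROS, "will be assessed preoperatively and postoperatively (30 days and 12 months) and will be compared between the suture groups as well as over time". Section {20a} lists the EQ-5D-5L variables as "EQ index range from 1 best to 5 worse and EQ-VAS scale value (0–100—best" and says of the secondary outcomes: "The outcomes will be analysed descriptively and compared between suture groups and between visits, where appropriate".

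The same section names the tests. For metric data a t-test "or one-way ANOVA will be used for metric data, if a normal distribution is assumed"; for nonparametric data a U-test "according to Wilcoxon–Mann–Whitney or to Kruskal–Wallis will be used". With two arms these are all simple group comparisons without a covariate. The section also sets the status of these results: "The test regarding the primary variable is considered confirmatory; all other tests are explanatory". Two-sided 95% confidence intervals are promised where appropriate.

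Baseline values enter in section {20b}, on additional analyses. It opens: "To identify relevant influencing factors (confounders), multivariate regression models will be considered". Its next sentence says that linear or logistic models will be implemented and that age, sex, BMI and "respective baseline values will be used as covariates to adjust for".

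**The concern.** Suturing time has no preoperative value, so the question arises only for secondary outcomes measured before surgery. For EQ index and EQ-VAS the preoperative score is collected from every patient, yet no between-arm test in {20a} uses it. Section {20b} does use it, but to search for confounders. In a randomised comparison that is not its main use: allocation is unrelated to the baseline score except by chance, and adjustment serves to gain precision and to remove chance imbalance. Section {16a} says that randomisation was not stratified by risk factors, so the analysis is the only place left to deal with such imbalance.

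At stake is the width of the intervals for the 30-day and 12-month arm differences. There is also a lesser question of precedence: an unadjusted and an adjusted result may both exist, and the article does not say which is the estimate for these scores.

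**Working it through.** **The plan's own figure.** Section {14} gives a sample size for suturing time only: difference 1.90 min, SD 4.00, two-sided 0.05, 80% power, 71 per arm. The noncentral t gives 70.55, rounded up to 71, with 80.3% power. With 5% drop-out, 71 / 0.95 = 74.7, so 75 per arm. The figure reproduces. It does not carry over to EQ index or EQ-VAS, for which the article states no target difference, SD or power.

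**Inputs.** Let ρ be the correlation between the preoperative and the follow-up value of the same score. The documents give none, so 0.2 to 0.7 is assumed. Equal SDs before and after surgery are also assumed; this matters only for the change-score column and the imbalance calculation.

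**Formulas.** Variance of the estimated arm difference, relative to an unadjusted t-test on follow-up values:
- follow-up values, unadjusted: 1
- change from baseline, unadjusted: 2(1 − ρ)
- linear model with arm and baseline (ANCOVA): 1 − ρ²

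The last is never the largest. It is at most 1, and 2(1 − ρ) − (1 − ρ²) = (1 − ρ)², which is never negative.

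| ρ (assumed) | Follow-up | Change | ANCOVA | CI width, ANCOVA vs follow-up | CI width, ANCOVA vs change |
|---|---|---|---|---|---|
| 0.2 | 1 | 1.60 | 0.96 | √0.96 = 0.980 (2% narrower) | √(0.96/1.60) = 0.775 (23% narrower) |
| 0.3 | 1 | 1.40 | 0.91 | √0.91 = 0.954 (5% narrower) | √(0.91/1.40) = 0.806 (19% narrower) |
| 0.5 | 1 | 1.00 | 0.75 | √0.75 = 0.866 (13% narrower) | √(0.75/1.00) = 0.866 (13% narrower) |
| 0.7 | 1 | 0.60 | 0.51 | √0.51 = 0.714 (29% narrower) | √(0.51/0.60) = 0.922 (8% narrower) |

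The one degree of freedom spent on the covariate is ignored; with about 140 patients it is negligible.

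**Chance imbalance.** With 71 per arm, the baseline difference between arms has a 95% range of ±1.96 × √(2/71) = ±0.33 SD. In an unadjusted follow-up comparison a fraction ρ of any imbalance is expected to pass into the arm difference: at ρ = 0.5, at most about 0.5 × 0.33 = 0.16 SD within that range. In a change comparison a fraction 1 − ρ passes through with the opposite sign. ANCOVA removes both.

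**The case against.** The strongest reply is that the requested model is already in the article. For a continuous score, a linear model that adjusts for its baseline value is ANCOVA, and the second sentence of {20b} describes just that, with age, sex and BMI added. This stands to the extent that a reader could not say the plan ignores baseline values. It does not settle the point: the models sit under additional analyses, are introduced as something to be considered, have confounder identification as their purpose, and are not made the between-arm estimate.

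A second reply is that the choice of model for an exploratory score belongs in the analysis plan, which is not shown. But {20a} does not leave the tests open. It names them, and a more precise method is available from data already collected.

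Several stronger readings are tempting and are not supported:
- A reader might infer that the tests are on postoperative values. Section {20a} does not say whether follow-up values or changes are compared; the conclusion holds for either.
- A reader might infer that a baseline imbalance passes in full into the result. Only the fractions shown in the working do.
- A reader might apply the 80% power at 71 per arm to quality of life and quote a gain in power. Those figures belong to suturing time.
- A reader might call the planned comparison invalid. An unadjusted comparison of randomised arms is valid; the loss is in precision.
- The variance factors are relative to a t-test. They do not carry over directly to the U-test that applies where normality is not assumed.

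The fear of selective emphasis is weak on its own, since the article labels the models in {20b} as additional.

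**Conclusion.** The point holds as a cheap improvement in efficiency, limited to EQ index and EQ-VAS at 30 days and 12 months. The named between-arm tests omit a preoperative value that the trial collects, and the adjusted model is not the stated estimate.

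The size rests wholly on an assumed correlation. Against a follow-up comparison the interval narrows by about 2% at 0.2, which is trivial, and by 13% at 0.5 and 29% at 0.7, which is useful. Against a change-score comparison the order is reversed, with the largest gain at low correlation.

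The outcomes are explicitly non-confirmatory, and neither the primary result nor the sample size is touched. The point does not extend to suturing time, length of stay or suture handling, which have no baseline value.

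**What to change.** In {20a}, state that the reported between-arm comparison of EQ index and of EQ-VAS, at 30 days and at 12 months, comes from a linear model with arm and the preoperative value of the same score, giving the adjusted difference with its 95% confidence interval. Keep the unadjusted summaries by arm as description, and the wider models of {20b} as exploratory.

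One further sentence is needed on missing baseline values. Section {20c} says that missing values are not replaced by estimates, so imputing the baseline covariate would contradict it as it stands. Either restrict the model to patients with a preoperative score, in line with that rule, or write an explicit exception for the baseline covariate.

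The cost is two or three sentences and no new data. Section {17a} unblinds the statistician only after database closure, and no interim analysis is planned, so the change should be documented before that point.

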### Trial design {8}

The BARGASTRO study is designed as a prospective, monocentric, randomized, two-arm parallel, active-controlled, superiority trial to compare a new unidirectional mid-term absorbable barbed (UBS) versus an absorbable traditional suture material (CS). A total of 150 patients are enrolled in one German clinic and randomly allocated in a 1:1 ratio to both suture groups. The surgical technique to create the gastro-jejunal as well as the jejuno-jejunal anastomosis will be standardized in both suture groups, and the participating surgeons are trained on the used suture technique. Patients will be kept unaware of the allocation (single blinded) until the completion of the study. After surgery, each subject will be examined on the day of discharge, 30 days, and 12 months postoperatively onsite at the hospital by surgeons performing the surgical procedure. This scheduled time has been selected because it represents the clinical routine setting of the participating hospital. Registration of the study has been performed in the platform for international clinical trials of the World Health Organization under http://www.clinicaltrials.gov NCT05433688 on 12 Oct. 2022. The local medical ethics committee responsible for the participating clinic approved the study on 15 March 2022 under project number D530/21. Our trial is reported in accordance with the SPIRIT guideline, which is a standard to publish study protocols [37]. The SPIRIT checklist is provided as an appendix, and a study flow chart is also included (Fig. 1).

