### Methods in analysis to handle protocol non-adherence and any statistical methods to handle missing data {20c}

All patients without a violation of the inclusion and exclusion criteria and who received the intended study treatment will be included in the primary analysis. Missing data/values will be analysed as such and will not be replaced by estimates. When reporting statistical distribution parameters, the number of non-missing values will be provided for transparency. Deviation from the study protocol will be assessed as protocol violations. If at least one inclusion or exclusion criterion is not fulfilled, the patient will be dropped out from the study.

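### For comparing visits within the same patients, the plan names only independent-groups tests plus an unspecified t-test, so within-patient correlation is ignored

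*Protocol article*

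**What the plan says.** All references are to the protocol article.

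- **Between-visit comparisons are planned.** Section {20a} closes its list of secondary outcomes with "The outcomes will be analysed descriptively and compared between suture groups and between visits, where appropriate". The abstract says that quality of life, taken preoperatively, at 30 days and at 12 months, "will be compared between the suture groups as well as over time". Section {12} plans over-time comparison of satisfaction, pain and quality of life too.
- **The same patients are measured each time.** Section {8} has every subject examined at discharge, 30 days and 12 months.
- **The tests named.** In {20a}: "For the analysis of binary data, a chi-square test will be used". Where outcomes are treated as nonparametric, rank tests "according to Wilcoxon–Mann–Whitney or to Kruskal–Wallis will be used". Besides a t-test of unstated type, "one-way ANOVA will be used for metric data, if a normal distribution is assumed". Section {20b} adds linear or logistic regression adjusted for age, sex, BMI and baseline values.
- **Number of arms.** Section {8} describes a "prospective, monocentric, randomized, two-arm parallel, active-controlled, superiority trial".
- **Missing visits.** Section {20c}: "Missing data/values will be analysed as such and will not be replaced by estimates".
- **Status.** In {20a}, only the test of the primary variable is confirmatory. Secondary variables are to be analysed descriptively, and all tests are two-sided at 5%.

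**The concern.** Measurements on one patient at different visits are usually positively correlated. Chi-square, Mann-Whitney U, Kruskal-Wallis and one-way ANOVA all treat the values being compared as coming from different people. Applied to visits, they leave the stable differences between patients in the error term, where a paired or repeated-measures analysis would remove them. The standard error of a change over time is then too large, the p-value is too large, and any confidence interval built the same way is too wide.

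What is at stake is the over-time part of the secondary results, which the abstract announces as an aim for quality of life. A real change between visits could be reported as not demonstrated. The article lists no alternative method for binary or non-normal outcomes, so an analyst who follows it literally has only independent-groups tests to use.

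**Working it through.** **The plan's own figure.** The article gives no figure for the between-visit comparisons; its only calculation is the sample size for the primary endpoint. With difference 1.90 min, SD 4.00, 80% power and two-sided 0.05, the two-sample t-test needs 70.55, so 71 per group, and 71/0.95 = 74.7, so 75. This reproduces, and nothing below changes it.

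**Inputs.** From the article: 150 patients, up to three visits per outcome, two-sided 5%. Assumed, because the article gives no value: within-patient correlation r = 0.3, 0.5 or 0.7, equal between all pairs of visits, and equal variances.

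**Two visits, comparison of means (if run unpaired).** The true SE of the mean change is SD × √(2(1−r)/n). The independent-samples formula uses SD × √(2/n). The ratio is 1/√(1−r).

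- Ratio: 1/√0.7 = 1.20; 1/√0.5 = 1.41; 1/√0.3 = 1.83.
- Actual type I error, 2 × [1 − Φ(1.96/√(1−r))]: cut-offs 2.34 / 2.77 / 3.58, giving 1.9% / 0.6% / 0.03%.
- Power for a change that has 80% power when paired (shift 1.96 + 0.84 = 2.80), 1 − Φ(1.96/√(1−r) − 2.80): 68% / 51% / 22%.

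These figures apply only if the unspecified t-test is run unpaired.

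**The tests the plan does name.** Simulation with 150 patients, three equally correlated normal visits and 3,000 replicates. The Monte Carlo standard error near 5% is √(0.05 × 0.95/3000) = 0.4 percentage points. The chi-square and McNemar rows compare the first with the last visit after a median split, without continuity correction.

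Type I error at nominal 5%:

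| Test | r = 0 | r = 0.3 | r = 0.5 | r = 0.7 |
|---|---|---|---|---|
| One-way ANOVA, 3 visits | 5.7% | 1.5% | 0.3% | 0.0% |
| Kruskal-Wallis, 3 visits | 5.6% | 1.5% | 0.2% | 0.0% |
| Chi-square, 2 visits | 5.7% | 3.5% | 1.9% | 0.6% |
| Repeated-measures ANOVA | 5.5% | 5.1% | 4.9% | 4.8% |
| Friedman | 5.2% | 4.7% | 5.1% | 4.1% |
| McNemar | 5.3% | 4.6% | 4.5% | 4.8% |

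A closed-form check on the ANOVA row: in large samples the statistic for three visits behaves as (1−r) times a chi-square on 2 degrees of freedom, so the type I error is 0.05^(1/(1−r)). This gives 0.05^1.43 = 1.4%, 0.05^2 = 0.25% and 0.05^3.33 = 0.005%, in line with the simulation. Chi-square is distorted less because dichotomising weakens the correlation.

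Power for a change of 0.2 SD from first to last visit, named test versus dependent-data test:

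| Comparison | r = 0.3 | r = 0.5 | r = 0.7 |
|---|---|---|---|
| One-way vs repeated-measures ANOVA | 23% vs 41% | 20% vs 59% | 12% vs 82% |
| Kruskal-Wallis vs Friedman | 22% vs 29% | 19% vs 43% | 11% vs 67% |
| Chi-square vs McNemar | 26% vs 32% | 26% vs 39% | 22% vs 48% |

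**The case against.** The strongest reply is that no sentence assigns these tests to the visit comparisons. Section {20a} lists tests by type of data, and the sentence on visits stands apart, after the outcome list, qualified by descriptive analysis and by appropriateness. The article is condensed, and an unseen analysis plan may name paired variants. This stands in part: the link is an inference. It is a fair one, because this is the only test list offered for comparisons that the article does plan.

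Four stronger readings are tempting, and the article does not support them.

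- **Kruskal-Wallis and one-way ANOVA can only be there for the visits.** Two arms make that a natural guess. But surgeon details are recorded ({18a}), BAROS defines five outcome groups ({12}) and influencing factors are to be explored ({20b}). Any of these could yield more than two independent groups. The article assigns neither use.
- **Every over-time comparison is wrong.** The primary test is called an independent samples t-test, whereas the secondary one is just a t-test, so a paired version for two visits is not excluded. McNemar's test is also a form of chi-square test, though the article does not name it.
- **False findings of change will result.** With positive correlation the error runs the other way.
- **Drop-out will look like change.** Leaving missing values as they are does mean that visits may contain different patients. But planned drop-out is 5% ({14}), reminders are in place ({18b}), non-missing counts will be reported, and nothing shows that selective loss would be material.

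The exploratory status limits the consequence, but it does not make a p-value from the wrong test correct.

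**Conclusion.** The point holds in a limited form. The plan compares visits within patients, and apart from an unspecified t-test it names only methods for independent groups. Followed as written, those methods are conservative. At assumed correlations of 0.3 to 0.7, nominal 5% tests run at about 1.5% down to practically zero for ANOVA and Kruskal-Wallis over three visits, and at 3.5% down to 0.6% for a two-visit chi-square. At r = 0.5, power for a 0.2 SD change is 20% for one-way ANOVA against 59% for repeated-measures ANOVA.

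The sizes rest on the assumed correlations, equal correlation between visits and normal data. The direction rests only on the correlation being positive. The confirmatory test of suturing time, the sample size and the comparison of arms at any one visit are untouched, so the conclusion about the suture is not at risk. What is exposed is the exploratory reporting of change over time.

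**What to change.** State in {20a}, or in the analysis plan, which methods apply to comparisons between visits:

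- metric outcomes: a paired t-test for two visits, or a repeated-measures mixed model using all available visits;
- ordinal or non-normal outcomes: Wilcoxon signed-rank for two visits, Friedman for three or more;
- binary outcomes: McNemar for two visits, Cochran Q for three or more.

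Keep the listed independent-groups tests for comparing arms at a single visit. They are valid there, and this point gives no reason to replace them with a model. Where a mixed model is used, it also lets patients with a missed visit contribute what they have, without replacing values.

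The cost is a few lines of text and slightly more programming. No new data are needed. The change should be fixed before the statistician is unblinded, which {17a} places after database closure.
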